### Progression criteria

The progression criteria to a full trial will be assessed against the rate of recruitment, with success defined as the recruitment of 50 patients into the feasibility trial.

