### Aims and objectives

There is a recognition that robust evidence must be produced before blood-derived therapies are further introduced into orthopaedic clinical practice [15]. These therapies are freely available in private practice and their use both in the UK and worldwide is increasing. No similar work currently exists to assess the efficacy of APS in treating shoulder pain. Further, to date, no randomised controlled trial (RCT) has investigated a comparison of CSI and APS for shoulder pain. The best means for evaluation of the clinical and cost-effectiveness of APS versus the current standard of care, CSI, would be to undertake a fully-powered multicentre RCT. However, there are uncertainties, specifically regarding recruitment rates and participant retention, that need to be assessed before undertaking a large-scale RCT.

This feasibility study trial aims to:Examine the conversion rate of eligible to randomised participants and total number of participants recruited.Investigate the levels of retention and data compliance at follow-up dates.Assess whether it is possible to collect the appropriate outcome measures (PROMIS Physical Function (upper extremity), PROMIS pain interference questionnaire[16], Oxford Shoulder Score (OSS) [17], Pain visual analogue score (VAS), EQ-5D-5L score [18], Work Productivity Impairment Questionnaire (WPAI) [19] and patient/hospital reported resource use including referral rates for shoulder surgery) at baseline, 3 months and 6 months.Gather data on any complications of either intervention at 6 months.

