### Primary outcome

The primary outcome is the feasibility and acceptability which will be assessed by the rate of patient conversion from eligibility for the study to randomisation. Numbers of screened ineligible patients will be noted to ensure recruitment for the main trial is feasible within this patient population. Numbers of screened eligible participants declining versus converted to randomised participants will be noted to ensure that the conversion rate of eligible to randomised participants is accurately estimated.

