### Statistical considerations and data analysis

Fifty participants will be recruited for this feasibility study. This sample size will be sufficient to estimate the rate of recruitment (i.e., participants randomised out of those screened) and retention.

Fifty participants should provide a robust estimate of the standard deviation around the PROMIS upper limb physical function to be used in the sample size calculation for a definitive trial. Specifically, to prepare for a definitive trial with an anticipated small standardised difference (0.1–0.3) and 80% power, a pilot study sample size of 40 participants (20 per arm) would be sufficient to estimate reliable input parameters for the sample size estimation of the definitive trial [20]; 50 participants will allow for up to 20% loss to follow-up.

The data analysis will be mainly descriptive for the feasibility trial, focussing on the primary outcome, i.e. the conversion rate of eligible to randomised participants, and the total number of participants recruited, as well as on retention and compliance data. Data on patient-reported outcomes, adverse events and complications will also be presented.

Descriptive statistics will be presented for all patient-reported outcomes at baseline and follow-up. Complications and adverse events/serious adverse events reported during the trial follow-up will also be summarised. Data will be presented by the treatment arm and overall. Mean and standard deviation (or median and interquartile range if non-normally distributed) for continuous variables and the number and percentage of participants in each group for binary or categorical variables will be presented.

Differences in outcomes between treatment arms at the follow-up time points will be presented as mean differences with corresponding 90% confidence intervals for continuous data, and risk differences and odds ratios with 90% confidence intervals for binary data, where appropriate. If sufficient outcome data are available, differences will be adjusted for the duration of symptoms (< = / > 6 months) and baseline scores for continuous variables, where applicable, and derived from multilevel mixed-effects linear or logistic regression models. If insufficient data are available, unadjusted differences will be presented.

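### The progression criterion calls a count of 50 recruited a rate, and leaves the primary outcome (conversion) and retention out of the formal definition of success

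*Protocol article*

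**What the plan says.** All references are to the protocol article.

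- **Progression criteria.** The section is one sentence. Progression is "assessed against the rate of recruitment, with success defined as the recruitment of 50 patients into the feasibility trial".
- **Statistical considerations and data analysis.** "Fifty participants will be recruited for this feasibility study". The number comes from a pilot-size rule under which "a pilot study sample size of 40 participants (20 per arm) would be sufficient to estimate reliable input parameters", and then "50 participants will allow for up to 20% loss to follow-up". The same section describes the rate of recruitment as randomised over screened.
- **Primary outcome.** Feasibility and acceptability are "assessed by the rate of patient conversion from eligibility for the study to randomisation". No threshold is attached.
- **Aims and objectives.** The reason for running a feasibility study is that "there are uncertainties, specifically regarding recruitment rates and participant retention, that need to be assessed before undertaking a large-scale RCT".
- **Secondary outcomes.** Loss to follow-up, missing data and withdrawal are to be measured, again without a threshold.
- **Trial oversight and management.** The Trial Management Group monitors the recruitment rate, but the article gives no target rate or recruitment period.

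**The concern.** The progression sentence announces a rate and then defines a number. A rate needs a denominator, either time or people approached, and the definition has neither. The number is also the trial's own enrolment target, which was derived to give enough data for estimating a standard deviation after dropout. It was not derived as a benchmark for feasibility.

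The definition also passes over what the study was set up to learn. Conversion is the primary outcome and retention is one of the two uncertainties named in the aims, yet neither can change whether the study is called a success.

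The decision on whether a definitive trial is worth funding is the main product of a feasibility study. If the formal rule is met while few eligible patients accept randomisation or few stay to 6 months, the word success will be attached to results that point the other way. Any weight given to conversion and retention would then be decided after the results are known.

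**Working it through.** **1. Where 50 comes from.** Inputs are 40 participants and 20% loss (Statistical considerations and data analysis). 40 / (1 − 0.20) = 50. The plan's figure is reproduced. It is a dropout-inflated sample size, and the same figure is then reused as the success threshold.

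**2. What the rule sees.** Its only input is the number recruited. The other quantities were varied with that number held at 50. The eligible counts, retained counts and durations are assumptions chosen to show the range. Intervals are exact (Clopper-Pearson) 95%.

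| Quantity | Illustrative result | Estimate (95% CI) | Formal rule |
|---|---|---|---|
| Conversion | 50/60 | 83% (71.5 to 91.7) | success |
| Conversion | 50/100 | 50% (39.8 to 60.2) | success |
| Conversion | 50/250 | 20% (15.2 to 25.5) | success |
| Conversion | 50/500 | 10% (7.5 to 13.0) | success |
| Retention | 45/50 | 90% (78.2 to 96.7) | success |
| Retention | 40/50 | 80% (66.3 to 90.0) | success |
| Retention | 25/50 | 50% (35.5 to 64.5) | success |

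The last row also misses the plan's own requirement. It leaves 25 participants with data, 15 short of the 40 said to be enough for estimating the inputs to the definitive sample size.

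**3. Why a time unit matters.** With two centres (Trial design and setting), recruitment per centre per month is 50 / (2 × months). That is 4.2 at 6 months, 2.1 at 12, 1.0 at 24 and 0.7 at 36. These are six-fold different speeds behind the same count. The durations are assumed, since the article states none.

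**4. How a retention threshold at the plan's own allowance would behave.** The plan allows 20% loss, so the natural anchor is at least 40 of 50 retained. With X ~ Binomial(50, p):

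| True retention p | P(X ≥ 40) |
|---|---|
| 60% | 0.002 |
| 70% | 0.079 |
| 80% | 0.584 |
| 90% | 0.991 |

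A cut at 40 separates poor from good retention well. At exactly the planned 80%, however, it would be missed with probability 1 − 0.584 = 0.416. A single pass/fail line there would be too harsh, and a middle zone is needed.

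**The case against.** The strongest reply has three parts.

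**The full protocol may say more.** The article condenses a full protocol (version 1.0) that is not shown, and a recruitment window is the kind of detail an article leaves out. This stands. A reader might infer that recruitment is open-ended, so that any trial left running until full must succeed. The article does not say that. If recruitment closes on a fixed date with fewer than 50, the criterion fails. The absence of a time window is therefore a remark about this article's wording only. The reply does not reach the rest of the point: the article states what success is, and that definition contains neither conversion nor retention.

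**The study still measures what matters.** Screening logs, numbers declining, loss to follow-up and withdrawal are all recorded, and the analysis is to focus on conversion, numbers recruited, retention and compliance. The Discussion says the results will guide a later funding decision, and nothing makes a definitive trial automatic once 50 are in. This stands too. A reader might infer that the study cannot tell a feasible definitive trial from an infeasible one. That is true of the one-sentence rule and not of the study, because poor retention would be visible in the report.

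**The size of the definitive trial proves nothing here.** With the plan's standardised difference of 0.1 to 0.3, 80% power and an assumed two-sided 5% level, n per arm = 2(1.960 + 0.842)²/d². This gives 350 to 3140 analysed, or 438 to 3925 randomised after 20% loss, which is about 9 to 79 times this study. It is tempting to offer that multiple as the size of the defect. It is not: the significance level is not in the article, the range of differences appears there only to justify the pilot size, and the definitive trial is envisaged as multicentre while this one has two sites.

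**Conclusion.** The point holds in a limited form. The progression criterion is worded as a rate but defined as a count equal to the planned sample size. It omits the primary outcome and one of the two uncertainties that the study exists to resolve. By its own terms it would declare success at 10% conversion as readily as at 83%, and at 50% retention as readily as at 90%.

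That conclusion needs no assumption beyond reading the sentence as written; the particular counts only illustrate it. The 0.584 assumes 50 randomised participants with independent retention at a true rate of 80%.

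No estimate is biased, no planned analysis is invalidated and the data needed are already collected, so this is a should-fix point and not a fatal one.

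**What to change.** Replace the sentence with a criterion in three parts:

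1. **Recruitment.** 50 randomised within the planned recruitment period, also expressed per centre per month. If the full protocol already states the period, cite it.
2. **Conversion.** Randomised over eligible, at or above a threshold that the sponsor sets and justifies. Keep this denominator distinct from the screened denominator used in the sample size paragraph.
3. **Retention.** The proportion of all randomised participants with a 6-month PROMIS physical function score, anchored at 80% from the plan's own loss allowance, with an amend zone below it. The documents give no lower limit for that zone, so the sponsor should choose and justify one. The denominator should be everyone randomised: the article's intention-to-treat population already requires data from at least one follow-up, so using it would overstate retention.

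Fix the thresholds before accumulating conversion and retention data are examined. Setting them merely before recruitment ends would let them be shaped by what the Trial Management Group has already seen. Report each component with its confidence interval, since 50 participants leave real uncertainty (66.3% to 90.0% around 40/50).

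The cost is one paragraph, with no extra participants or measurements. The drawback is that the trial can then fail its own criterion on conversion or retention even after recruiting all 50.

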## Discussion

Shoulder pain is common, and its treatment represents a challenge. Shoulder pain has a significant effect on the individuals’ activities of daily living. One of the mainstays of treatment for this condition is a CSI into the shoulder, but the evidence around the medium-term efficacy of this treatment is absent. Further, the evidence around the use of APS injection is underdeveloped but potentially represents an effective treatment for a large number of patients with subacromial pain. This feasibility will guide the appropriateness or otherwise of funding a fully-powered intervention trial comparing CSI and APS.

## Data Availability

Not applicable.
